### Eligibility criteria

The target population is adults aged 60 years and older who are either frail or pre-frail (as defined by the Fried Frailty Criteria), reporting walking difficulties/slow walking, and low protein intake (<1 g protein/kg BW/day). The full eligibility criteria are described in
Table 1.

**Table 1. T1:** Eligibility criteria.

Inclusion criteria
Aged 60 years and older. Frail (at least 3 criteria) or pre-frail (1-2 criteria) as defined by the Fried Frailty criteria ^ 17 ^. This must include slow walking speed (or difficulty walking). Low protein intake (<1 g protein/kg body weight/day) measured by the average of two 24-hour dietary recall assessments. Willing and able to provide informed consent to participate.
Exclusion criteria
Dementia or cognitive impairment (defined as an Abbreviated Mental Test (AMT) score of 6 or less). Inability to walk 3 m without assistance (walking aid permitted). Unable to follow verbal instructions that would make participation in the exercise group impractical including severe hearing impairment not corrected by a hearing aid or inability to follow simple safety instructions ( *e.g.*, English comprehension). Living in a residential care or nursing home. Pre-existing diagnosis of: ▪ Stroke in the last 6 months. ▪ Parkinson’s Disease. ▪ Acute, unstable physical illness that would make participation in the exercise programme unsafe. ▪ Dysphagia or swallowing problems that requires a modified diet. ▪ Type 1 diabetes or Type 2 diabetes on insulin. ▪ Severe kidney disease (stage 4 or 5). Already taking protein supplements or known allergies to ingredients of protein supplement (milk, soya) or lactose intolerant. Poor kidney function defined by an Estimated Glomerular Filtration Rate (eGFR) of <30 mL/min/1.73m2 (blood test). High risk of developing refeeding problems based upon items from NICE guidance ( https://www.nice.org.uk/guidance/cg32).

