The exercises performed during the supervised group sessions are also undertaken at home. Participants are asked to complete the programme at home once a week while attending the group sessions. Then, twice per week for a further eight weeks of independent exercise (with three support phone calls). During group discussions and support phone calls, we help participants make a long-term exercise plan. This includes continuing with their home exercises but also considering other activities they may undertake include digital options. Participants will be given access to an existing exercise app (Good Boost:
https://www.goodboost.ai/). Use of the app is completely optional and as part of this feasibility study, we are interested to see how many participants opt to use this type of offering.

**
*Protein supplements.*
** Participants randomised to receive protein supplements will be asked to take the supplements for 24 weeks starting on the day they begin the group exercise sessions. The protein is a powdered supplement (Nutricia Fortifit) produced by Danone Nutricia Research and delivered to participants’ homes. Cold water is added to make up a drink in a shaker (125 ml water per serving). Each serving of the protein powder contains 149 kcal, 20.7 g whey protein, 2.8 g leucine, 20 ug/800 IU vitamin D and 501 mg of calcium. This product has been chosen as it is enriched with leucine, allowing more effective muscle protein synthesis stimulation in a lower serving
^
36
^, and is less calorific than using a pre-prepared protein drink. The main target of the intervention is to increase protein intake rather than energy.

Physiotherapists will provide the supplement to participants with the support of the central study team dietitian. Protein supplements are tailored to each participant based on their baseline protein intake. The aim is for each participant to consume up to 1.6 g protein/kgBW/day. This is slightly higher than the recommended daily protein intake for older adults with acute or chronic diseases to maintain or regain muscle mass (1.2 – 1.5 g protein/kgBW/day)
^
5
^. However, retrospective breakpoint analysis conducted on RCTs exploring the impact of protein supplementation on resistance training-induced gains in fat-free mass (FFM) demonstrated that increases in FFM plateaued at daily protein intakes of 1.6 g/kg/d
^
37

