^. If a participant has a BMI of 30 or more, then the recommended dose of protein is 75% of the calculated amount based on weight (as per usual clinical practice)
^
38
^. Additionally, if a participant has an eGFR between 30-60 ml/min/1.73 m
^2 ^(indicating a moderate reduction in renal function), protein intake will be limited to 1.3 g/kgBW/day. This is the maximum dose recommended for this patient group by The Kidney Disease Improving Global Outcomes (KDIGO) guidelines.

On a day when participants undertake Mobility and Strength training (at the hospital or at home), they will be advised to take one of their drinks of the supplement directly after the exercise session. Participants will complete a protein supplement diary to monitor adherence and record any side-effects experienced. Participants will be monitored and weighed at regular reviews (
Table 3). If a participant is experiencing gastro-intestinal problems, then they will be advised to reduce the dose by a half and gradually increase the dose back to the recommended amount over four days to improve tolerance. If a participant has lost >10% of their weight or is reporting ongoing intolerance issues, then participants will be reviewed by the main study team dietitian to decide if the protein supplement dose needs to be adjusted or other dietary advice given.

The chosen supplement also contains vitamin D and calcium. If participants are already taking over the counter supplements, then they will be asked to stop taking them while they are on the protein supplements. If participants are already on prescribed supplements, then the physiotherapist will liaise with the participant’s general practitioner to adjust their prescription to ensure daily maximum doses are not exceeded (Vitamin D: maximum of 4,000 IU per day; Calcium: maximum of 1 g per day).

All participants will attend the same exercise sessions. Supplement reviews will be conducted outside these sessions and participants will be asked not to discuss them in the groups. Groups will be run this way to so sites can fill the exercise groups in a timely way.

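### For unadjusted participants of 69 kg or more, reaching 1.6 g/kg protein takes enough trial powder to exceed the stated 1 g/day calcium maximum on its own

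*Protocol article*

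**What the plan says.** All the dosing figures stand in the Protocol article, Interventions, under Protein supplements.

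- **Content per serving:** "20.7 g whey protein, 2.8 g leucine, 20 ug/800 IU vitamin D and 501 mg of calcium".
- **Aim:** "The aim is for each participant to consume up to 1.6 g protein/kgBW/day". This is total intake, diet plus powder, and "Protein supplements are tailored to each participant based on their baseline protein intake".
- **Reductions:** 75% of the calculated amount at a BMI of 30 or more, and a limit of 1.3 g/kg/day at an eGFR of 30 to 60. Later dose changes are for gastrointestinal intolerance or weight loss. No rule limits servings because of calcium.
- **Calcium and vitamin D:** the paragraph begins by noting that the powder itself contains both. Over-the-counter products are to be stopped. For prescribed ones, the physiotherapist works with the general practitioner to "adjust their prescription to ensure daily maximum doses are not exceeded", with the limits in parentheses: "Vitamin D: maximum of 4,000 IU per day; Calcium: maximum of 1 g per day".

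The Eligibility criteria (Table 1) require "Low protein intake (<1 g protein/kg body weight/day) measured by the average of two 24-hour dietary recall assessments".

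**The concern.** The calcium rule works only on what participants take besides the trial product. If the powder, at the number of servings implied by the protein aim, already passes 1 g of calcium, no change to other supplements can bring the participant back under the limit.

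The person arranging the supplement would then hold two stated figures that cannot both be met, with nothing in the article to say how they combine. A stated safety limit is involved, in frail or pre-frail older people who take the product daily for 24 weeks. The feasibility measures would not show how the conflict was handled: the supplement criteria in Table 4 count home delivery as planned and days on which supplements were taken, not servings per day.

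**Working it through.** **Inputs from the article:** 20.7 g protein, 501 mg calcium and 800 IU vitamin D per serving; aim 1.6 g/kg/day; baseline intake below 1.0 g/kg/day; limits of 1 g calcium and 4,000 IU vitamin D per day. The article states no number of servings and no calcium total, so there is no figure of its own to reproduce.

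**Assumption:** dietary protein stays at its baseline level. Dietary calcium is not counted.

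**Step 1. Calcium by whole servings.**

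| Servings | Protein (g) | Calcium (mg) | Vitamin D (IU) |
|---|---|---|---|
| 1 | 20.7 | 501 | 800 |
| 2 | 41.4 | 1,002 | 1,600 |
| 3 | 62.1 | 1,503 | 2,400 |

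Two servings meet the calcium figure apart from 2 mg (0.2%), which is rounding. The vitamin D limit is reached only at 4,000 / 800 = 5 servings, so calcium is the limit that binds.

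**Step 2. Who needs more than two servings, with no BMI or eGFR reduction.**

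Servings = (1.6 − intake) × weight / 20.7. This exceeds 2 when weight > 41.4 / (1.6 − intake).

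- Intake 1.0 g/kg (the eligibility bound): 41.4 / 0.6 = 69.0 kg
- Intake 0.9 g/kg: 41.4 / 0.7 = 59.1 kg
- Intake 0.8 g/kg: 41.4 / 0.8 = 51.75 kg

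Every eligible participant eats less than 1.0 g/kg, so the gap is always more than 0.6 g/kg. At 69 kg or more, all unadjusted participants need more than two servings, whatever their intake. This rests on the article's figures and the constant-diet assumption; it needs no assumed distribution.

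**Step 3. Example: 70 kg, 0.8 g/kg.**

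- Gap: 0.8 × 70 = 56 g
- Servings: 56 / 20.7 = 2.71
- Calcium: 2.71 × 501 = about 1,355 mg (1,503 mg if three whole servings)
- With two servings instead: 41.4 / 70 = 0.59 g/kg added, giving a total of about 1.39 g/kg

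**Step 4. The same participant under the reduced targets.**

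- eGFR rule: (1.3 − 0.8) × 70 / 20.7 = 1.69 servings, about 847 mg. More than two servings are needed only above 41.4 / 0.5 = 82.8 kg at 0.8 g/kg, or above 41.4 / 0.6 = 69.0 kg at 0.7 g/kg.
- BMI rule, 75% applied to the 1.6 target: (1.2 − 0.8) × 70 / 20.7 = 1.35 servings.
- BMI rule, 75% applied to the supplement amount: 0.75 × 56 / 20.7 = 2.03 servings.

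The conflict is less frequent here, but not absent.

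**Step 5. Illustration of frequency, on assumed distributions only.** Weight was taken as normal with mean 60 to 75 kg and SD 11 (kept between 40 and 100 kg). Intake was taken as normal with mean 0.70 to 0.85 g/kg and SD 0.15 (kept between 0.3 and 1.0). Between 71% and 98% of simulated participants on the unadjusted target then need more than two servings. None of these means or SDs comes from the article, and the simulation does not remove people to whom the BMI or eGFR rule would apply.

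**The case against.** The strongest reply concerns scope. The 1 g figure appears once, in parentheses, in the sentence on prescribed supplements. It is not written as a cap on servings, and a participant on no other supplement receives no calcium instruction at all. It might have been meant only for calcium from outside the trial. The ambiguity is real, but it does not dissolve the conflict. The paragraph begins from the powder's own calcium, the figure is called a daily maximum dose, and nothing excludes the powder from it. Even within the prescribed-supplement rule, cutting the prescription to zero leaves the participant over 1 g above two servings.

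A second reply is that the wording of the aim sets a ceiling, so a lower dose breaches nothing. That softens the clash. Yet 1.6 g/kg is stated as the aim and justified by the intake at which gains in fat-free mass levelled off, and calcium is not among the stated reasons to go below it.

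A third is that training, central dietitian support and the study manual may settle the matter in practice. They may. A detailed dosing table would also normally sit in the manual, so its absence from the article is no fault. The point is that figures printed in the article do not fit together.

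A reader might go further and infer the following, which the document does not support:

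- **That only one serving is permitted.** This turns on the 2 mg excess at two servings. Two servings leave the 70 kg example near 1.39 g/kg, so a collapse of the protein contrast does not follow.
- **That much of the arm is affected.** The share on the unadjusted target is unknown, as are weights and intakes.
- **That the delivered dose cannot be interpreted.** Supplement diaries, review logs and a dietary protein assessment at 8 months are planned, and this is a feasibility trial whose supplement criteria do not depend on g/kg achieved.

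**Conclusion.** The conflict holds on the article's own figures. For unadjusted participants of 69 kg or more at any eligible intake, and from lower weights at lower intakes, the powder needed to reach 1.6 g/kg carries more calcium than the stated daily maximum. The example overshoots by about 355 mg (1,355 − 1,000), or about 503 mg if three whole servings are taken.

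This rests on constant dietary protein and on the maximum counting calcium from the powder, which the text suggests but does not state. If it also covers calcium from food, the excess is larger. If it was meant only for calcium from outside the trial, the article needs to say so. How many participants are affected cannot be derived from the document. Because a stated safety limit is involved and clarification is cheap, it should be settled. Nothing here shows which figure is right.

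**What to change.** The study dietitian and the group with safety oversight (the article names an Independent Monitoring Committee) should reconcile the protein aim, the per-serving calcium content and the calcium maximum. The text should then state:

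1. whether the 1 g maximum includes calcium from the trial powder;
2. how the maximum and the protein aim apply together when they conflict, including for participants who take no other supplement.

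The choice is a clinical one, and no dose or limit is proposed here. The cost is a short clarification of the protocol, carried into the study manual and passed to sites. The article reports recruitment as ongoing, so sites already providing the supplement would need the clarification too.

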### Training

Site research staff who are responsible for screening, consenting and data collection will attend approximately 6 hours of training to cover all aspects of the trial and processes involved. Physiotherapists delivering the interventions will attend a full day of training to learn how to deliver the group sessions, prescribe and monitor provision of protein supplements and to complete study related administration. All staff will receive a detailed study manual.

### Primary feasibility outcomes

**
*Progression criteria.*
** Progression criteria into a future definitive trial will be based on the stop-go criteria assessing feasibility detailed in
Table 4 alongside consideration of adverse events and discussions with the Independent Monitoring Committee. The stop-go criteria follow a ‘traffic light’ system: Red (stop), Amber (proceed with modifications) and Green (Go). There are four categories: recruitment, intervention fidelity, intervention adherence and study retention.

**Table 4. T4:** Stop-Go Criteria.

	Red	Amber	Green
Recruitment: Number of participants recruited	< 25 participants recruited within 6 months	25–39 participants recruited within 6 months	>40 participants recruited within 6 months
Intervention fidelity: provision of the mobility and strength training	<50% undergo their individual assessment and are allocated to their group sessions	50% – 80% of participants undergo their individual assessment and are allocated to their group sessions	>80% of participants undergo their individual assessment and are allocated to their group sessions
Intervention fidelity: delivery of the mobility and strength training (fidelity assessment *via* observations based on core criteria checklist)	<50% of all key criteria are met during observed sessions	50–80% of key criteria are met during observed sessions	>80% of key criteria are met during observed sessions
Intervention fidelity: protein supplements	<50% of participants receive the protein supplements *via* home delivery as intended	50–80% of participants receive the protein supplements *via* home delivery as intended	>80% of participants receive the protein supplements *via* home delivery as intended
Intervention adherence: participant attendance at the mobility and strength training	On average, < 8/16 sessions (50%) of sessions attended by 70% or more participants	On average, 8-10/16 session (50–69%) of sessions attended by 70% or more participants	On average, at least 11/16 sessions (70%) attended by 70% or more of participants
Intervention adherence: participant adherence to the protein supplements	On average, 70% or more participants report taking protein supplements on <50% of days over 24 weeks	On average, 70% or more participants report taking protein supplements on 50–70% of days over 24 weeks	On average, 70% or more participants report taking protein supplements on ≥70% of days over 24 weeks
Study retention: follow up rates and checking for differential loss to follow up	>30% loss to follow up at 8 months in either study arm.	29–15% loss to follow up at 8 months in either study arm.	<15% loss to follow up at 8 months in both study arms.

Recruitment: We will collect data on screening and recruitment of eligible patients from each site on a monthly basis alongside reasons for exclusion.

Intervention fidelity: Physiotherapists will record intervention provision on an intervention log, which will be monitored to assess treatment fidelity. We will also observe or record intervention sessions and assess the delivery of the interventions using a checklist of the core criteria of the intervention. We will monitor protein supplement delivery to ensure supplements are delivered to participants as intended. The central study team will also visit up to 20% of participants at home to observe home exercises and check on protein supplement intake.

Adherence with the intervention: Attendance at the exercise classes is monitored using intervention logs completed by the physiotherapists. Participants will be asked to record when they take the protein supplements in their supplement diary.

Study retention: Follow up rates will be collected, and we will evaluate if there is any differential loss to follow up by study group.

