## Abstract

Background Frailty is a common syndrome affecting older people and puts them at risk of hospitalisation, needing care or death. First signs of frailty include reduced muscle strength and mobility decline. A key cause of mobility decline as we age is sarcopenia (age related reduction in muscle strength and mass). Poor nutrition contributes to sarcopenia. A shortfall in protein is associated with reduced muscle mass and strength. This may be due to inadequate intake but also because older people have higher protein needs, especially those with multimorbidity. We need to develop effective treatment to reduce or slow the onset of frailty and mobility decline. Exercise is a recommended treatment. Protein supplements to address the shortfall in protein have the potential to enhance the benefit of regular exercise in frail or pre-frail older adults. This has yet to be definitively demonstrated. Aim To establish the feasibility of conducting an RCT evaluating mobility and strength training with or without protein supplements for people over 60 years old who are frail or pre-frail with a low protein intake. Methods A multicentre, parallel, 2-group, feasibility RCT. Participants (recruitment target = 50) with problems walking, low protein intake and classified as frail or pre-frail will be recruited from four NHS Physiotherapy community services. Participants will be randomised (secure computer-generated: 1:1) to receive 24 weeks of mobility and strength training (delivered in 16 group sessions plus home exercises) or 24 weeks of mobility and strength training with daily protein supplements. Primary feasibility objectives are to estimate 1) ability to screen and recruit eligible participants, 2) intervention fidelity, adherence, and tolerance and 3) retention of participants at follow up. Secondary objectives are to 1) test data collection procedures, 2) assess data completeness and 3) confirm sample size calculation for a definitive RCT. Registration ISRCTN Registry (ISRCTN30405954; 18/10/2022).

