### Sample size

Given this is a feasibility study to inform the design of a definitive study, the sample size was determined from a recent simulation study of sample size requirements in pilot RCTs
^
39
^. A total of 50 measured subjects are recommended to calculate key design parameters (namely, standard deviation around the primary outcome measure for a definitive trial) and subsequently establish the definitive study sample size. Therefore, the target sample size for this study is 50 patients.

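### In the attendance row of Table 4, the Green threshold of 11/16 sessions is 68.75%, not the stated 70%, so count and percentage can give the row different results

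*Protocol article*

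**What the plan says.** Under Primary feasibility outcomes, the article states: "Progression criteria into a future definitive trial will be based on the stop-go criteria assessing feasibility detailed in" Table 4, to be read together with adverse events and discussion with the Independent Monitoring Committee. Green means go, Amber means proceed with modifications, and Red means stop.

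The attendance row gives each colour a count of sessions and a percentage:

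- Red: "On average, < 8/16 sessions (50%) of sessions attended by 70% or more participants"
- Amber: "On average, 8-10/16 session (50–69%) of sessions attended by 70% or more participants"
- Green: "On average, at least 11/16 sessions (70%) attended by 70% or more of participants"

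The denominator is fixed by the design; the Abstract describes the training as "delivered in 16 group sessions plus home exercises". The other adherence row, for supplements, has as its Green cell: "On average, 70% or more participants report taking protein supplements on ≥70% of days over 24 weeks". That row gives no count.

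**The concern.** A progression rule stated in two ways must give the same answer both ways. Here it does not at the Green/Amber boundary: the count that opens Green converts to a percentage that the adjacent cell assigns to Amber. The article neither ranks the two definitions nor calls the percentages approximate, so whoever tabulates attendance has to choose between them. At stake is whether this row reads as go or falls short of it. If the choice is still open once the attendance data are known, the row is not a fully pre-specified criterion near its boundary.

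**Working it through.** **Inputs from the article.** 16 group sessions (Abstract; Table 3; Table 4). Count bands <8, 8–10 and ≥11, with percentage labels 50%, 50–69% and 70% (Table 4). Participant share required: 70% or more (Table 4). Target sample size 50 (Sample size: "the target sample size for this study is 50 patients").

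**Step 1. Convert the counts (sessions / 16 × 100).**

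| Sessions | Percentage | Band by count | Band by percentage label |
|---|---|---|---|
| 7 | 43.75 | Red | Red |
| 8 | 50.0 | Amber | Amber |
| 10 | 62.5 | Amber | Amber |
| 11 | 68.75 | Green | Amber (50–69%) |
| 12 | 75.0 | Green | Green |

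The printed equality 11/16 = 70% does not reproduce. In the other direction, 0.70 × 16 = 11.2, so the first whole number of sessions to reach 70% is 12. Rounding does not help: 68.75% rounds to 69%, the upper limit printed for Amber. Eleven is the only whole number of sessions on which the two definitions disagree.

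**Step 2. When the row's result changes.** Read the cell as the share of participants who reach the threshold. The row is Green by count if at least 70% attend ≥11 sessions, and Green by percentage if at least 70% attend ≥12. The results differ when the first holds and the second does not.

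Constructed example with 50 participants: 30 attend 12 sessions, 8 attend 11 and 12 attend 6. By count, (30 + 8)/50 = 76% reach the threshold, so the row is Green. By percentage, 30/50 = 60% reach it, so the row is not Green.

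If the cell is instead read as mean attendance, a mean from 11.0 to just under 11.2 sessions (68.75% to just under 70%) is Green by count and not Green by percentage.

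**Step 3. How likely a disagreement is.** The article gives no expected attendance, so this step rests on assumptions: 50 participants, independent of one another; Green needs at least 0.70 × 50 = 35 of them; each participant's sessions attended follow a binomial(16, p) at correlation 0, or a beta-binomial with mean p and within-person correlation ρ, with parameters p(1−ρ)/ρ and (1−p)(1−ρ)/ρ. Let P11 and P12 be the probabilities that a participant attends ≥11 and ≥12 sessions. The chance of Green is P[Binomial(50, P11) ≥ 35] by count and P[Binomial(50, P12) ≥ 35] by percentage.

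| Mean attendance p | ρ | P11 | P12 | Green by count | Green by percentage |
|---|---|---|---|---|---|
| 0.70 | 0 | 0.660 | 0.450 | 0.33 | 0.00 |
| 0.75 | 0 | 0.810 | 0.630 | 0.98 | 0.19 |
| 0.80 | 0 | 0.918 | 0.798 | 1.00 | 0.97 |
| 0.85 | 0 | 0.976 | 0.921 | 1.00 | 1.00 |
| 0.70 | 0.2 | 0.620 | 0.533 | 0.16 | 0.01 |
| 0.75 | 0.2 | 0.705 | 0.624 | 0.60 | 0.17 |
| 0.80 | 0.2 | 0.784 | 0.716 | 0.94 | 0.66 |
| 0.85 | 0.2 | 0.856 | 0.803 | 1.00 | 0.97 |

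At ρ = 0.2 the gap is 14, 43, 28 and 3 percentage points at 70%, 75%, 80% and 85% attendance. At ρ = 0.3 and 75% attendance the figures are 0.55 v 0.22.

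**The case against.** The best defence is that the counts already form a complete rule. Attendance is logged as a whole number of sessions, and <8, 8–10 and ≥11 cover every value without overlap. Eleven is the nearest whole number to 11.2, the percentages stand in brackets after the counts, and a reader could take them as loose labels. Much of this stands: a workable rule is on the page. But the article never says that the count governs, and Amber is given 69% as its upper end, which is what 11/16 rounds to. A loose 70% would pass if the neighbouring cell did not claim that value.

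The stakes are also limited. This is one of seven rows in the table, the committee weighs it with other evidence, and no hypothesis test, sample size or effect estimate depends on it.

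Some stronger readings are tempting and are not supported:

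- A reader might infer that someone who attends 11 sessions is both Green and Amber. Colours belong to the row; a participant only counts towards a threshold or does not.
- A reader might infer that data failing Green by percentage are Amber. As worded, Amber needs 70% or more of participants in the 50–69% band. In the example above, 60% reach 70% of sessions, 8/50 = 16% fall in 50–69% and 12/50 = 24% fall below 50%, so no cell is literally met. Amber follows only if the bands are read cumulatively, which the article does not state. The safe conclusion is not Green.
- A reader might take the contrast at 75% attendance as typical. It is the largest of the four attendance levels tabulated.
- A reader might infer that both adherence rows must share a 70% standard, so that 12/16 is the right cut-off. The article does not require this.

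**Conclusion.** The point holds. The printed percentage for the Green attendance threshold is wrong, and it conflicts with the Amber band beside it. This is more than a clerical slip, because the threshold decides a progression row and the two definitions can give different results on the same data. The arithmetic rests on the article alone.

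The size of the effect rests on the assumed attendance model. The row is exposed when attendance lies near the boundary, and the disagreement nearly vanishes at 85% mean attendance. Nothing in the article suggests that a choice between the definitions after seeing the data is planned; the wording simply leaves it open.

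**What to change.** Before attendance is tabulated, correct the row so that count and percentage agree, and state which one governs.

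The smallest change keeps the counts and relabels them: Red fewer than 8/16 (<50%), Amber 8–10/16 (50–62.5%), Green at least 11/16 (about 69%).

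If a true 70% standard was intended, Green must become at least 12/16 (75%, the first whole number at or above 70%) and Amber 8–11/16 (50–69%), with Red unchanged. The downside is that Green is then somewhat harder to reach.

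Either version is a one-line correction to Table 4 and needs no new data.

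### The supplement-adherence row of Table 4 counts days of use with no condition on amount, so it can be Green with well under half of the tailored supplement protein taken

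*Protocol article*

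**What the plan says.** The stop-go table (Protocol article, Primary feasibility outcomes, Table 4) has one row for adherence to the supplements. Its Green cell is "On average, 70% or more participants report taking protein supplements on ≥70% of days over 24 weeks". Amber and Red use the same unit, the percentage of days. The source is the participant's diary: "Participants will be asked to record when they take the protein supplements in their supplement diary".

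The Interventions section defines the dose as an amount. It is set individually: "Protein supplements are tailored to each participant based on their baseline protein intake". The ceiling for total intake is stated next: "The aim is for each participant to consume up to 1.6 g protein/kgBW/day". The content of a serving, in which the last item is calcium, is given as follows: "Each serving of the protein powder contains 149 kcal, 20.7 g whey protein, 2.8 g leucine, 20 ug/800 IU vitamin D and 501 mg of". Two adjustments apply: "If a participant has a BMI of 30 or more, then the recommended dose of protein is 75% of the calculated amount based on weight", and total intake is limited to 1.3 g/kgBW/day when eGFR is 30-60. On exercise days one of the participant's drinks is to follow the session, which implies more than one drink a day. Participants with gastro-intestinal problems are told to "reduce the dose by a half and gradually increase the dose back to the recommended amount over four days".

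Eligibility (Table 1) requires "Low protein intake (<1 g protein/kg body weight/day) measured by the average of two 24-hour dietary recall assessments".

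**The concern.** The intervention is defined in grams of protein per kilogram per day, but its adherence criterion is defined in days. When the prescription is several servings, a day count cannot tell one drink from three, or a full dose from a half dose.

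No other row of Table 4 covers the amount taken. The home-delivery row concerns what arrives at the house. Dietary protein is scheduled in Table 2 only at baseline and at 8 months (8/12 x 52 = about 35 weeks), which would normally fall after a 24-week course has ended. Home visits to check intake cover up to 20% of participants.

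The arms differ only in the supplement, and the Introduction presents tailored provision as a remedy for a weakness of previous trials. Whether participants take the tailored amount is therefore a question the feasibility trial should answer, and a Green on this row does not answer it.

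**Working it through.** The article states no number of servings per day and no share of dose taken, so there is no figure of its own to reproduce.

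**Inputs from the article:** ceiling for total protein 1.6 g/kg/day; 20.7 g per serving; baseline intake below 1 g/kg/day; Green at 70% of days (0.70 x 168 = 117.6, so 118 days); renal limit 1.3 g/kg/day; 75% rule at BMI of 30 or more.

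**Assumed, because not given:** body weight and actual baseline intake. Central case 70 kg and 0.8 g/kg/day; range 60-80 kg and 0.6-0.95 g/kg/day.

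**Step 1. Is the dose more than one serving?** With the 1.6 target and no adjustment, the gap exceeds 1.6 - 1.0 = 0.6 g/kg/day. It is more than one serving for anyone above 20.7/0.6 = 34.5 kg. In the central case the gap is (1.6 - 0.8) x 70 = 56 g/day, and 56/20.7 = 2.7 servings.

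**Step 2. Half dose at the Green threshold.** 0.50 x 0.70 = 35% of the intended supplement protein. Weight and baseline cancel out.

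**Step 3. One serving at the Green threshold.** Average supplement protein is 0.70 x 20.7 = 14.49 g/day. Divided by the gap:

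| Weight, baseline, target (g/kg/day) | Gap (g/day) | Share |
|---|---|---|
| 70 kg, 0.8, 1.6 | 56 | 26% |
| 60 kg, 0.95, 1.6 (one end of range) | 39 | 37% |
| 80 kg, 0.6, 1.6 (other end) | 80 | 18% |
| 70 kg, 0.8, 1.3 (renal limit) | 35 | 41% |

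One serving on every day in the central case is 20.7/56 = 37% of the intended amount and scores 100% of days.

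**Step 4. Where the gap between days and dose narrows.** Under the renal limit, the same 60-80 kg and 0.6-0.95 range gives 14.49/56 = 26% to 14.49/21 = 69%. At the upper end the dose is about one serving, and a day count works well. For BMI of 30 or more, with an assumed 85-105 kg and baseline 0.6-0.9, the dose is 2.2-3.8 servings (share 18-32%) if the 75% is applied to the gap, and 1.2-3.0 servings (23-57%) if applied to the target.

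**Step 5. From participant to row.** These shares are for a participant who meets the day condition. With 25 per arm, Green needs 0.70 x 25 = 17.5, so 18 such participants. The row places no condition on the rest. If they took none and doses were equal, the arm minimum with half-dosing would be 0.70 x 35% = 24.5%.

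**The case against.** The strongest objection is that this is a condensed article. It does not say that a part-dose counts as an adherent day. The diary may record each drink, and the supplement review logs in Table 2 may record amounts. How a diary entry becomes an adherent day could be defined in the full protocol, the analysis plan or the diary, none of which is shown. This stands in part: if servings are already recorded, only the wording needs to change. It does not remove the point, because the row is a stated decision rule in days. The home-delivery row of the same table does carry a qualifier that delivery was as planned; this row has none.

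The sizes depend on assumptions. The article gives no weights, no mean baseline intake and no serving count, and 1.6 g/kg/day is a ceiling. A reader might infer that a Green row means about a quarter of the protein is being taken. The article does not support that. The quarter belongs to one assumed case, needs exactly one drink on exactly 70% of days, and concerns supplement protein only. Total intake in that case would be (56 + 14.49)/70 = 1.01 g/kg/day, or 63% of 1.6.

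A reader might also infer that poor tolerance goes unseen. That is too strong. The diary records side-effects, reviews are scheduled at weeks 2, 4, 8, 12 and 16 and at three later calls, ongoing intolerance goes to the dietitian, and severe or lasting symptoms are reportable. Halving is meant to be brief. What stands is narrower: this row does not reflect reduced dosing.

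Finally, one Green row does not decide progression, which also weighs adverse events and discussion with the Independent Monitoring Committee. A claim that the definitive trial would go ahead with too little dose to separate the arms is not supported.

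**Conclusion.** The point holds in this form: the row measures frequency of use, while the intervention is an individually tailored amount. The result that needs no assumption about participants is that a half dose on 70% of days, 35% of the intended supplement protein, meets the Green condition. The one-serving figures (26% in the central case, 18-37% over the assumed range, about 41% with the renal limit at 70 kg and 0.8 g/kg/day) rest on assumed weight and baseline intake, on dosing up to the 1.6 or 1.3 figure, and on the plain reading that any reported use makes a day count. All are floors that the rule allows, not forecasts. The shortfall is smaller or absent where the tailored dose is close to one serving. The criterion should be changed, because it is one of the rules on which progression is judged and the change is cheap.

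**What to change.** Score the Table 4 row as servings taken divided by servings prescribed over the 24 weeks, per participant, from the supplement diary and review logs. Fix the cut points in advance. The existing 50% and 70% can be kept, but as a deliberate choice, since they would now apply to a stricter quantity: the half-dose pattern (35%) and the central one-serving-daily pattern (37%) would both fall below 50%. Report days with any intake alongside.

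Report dose reductions separately, and show intake relative both to the dose in force and to the originally calculated dose. The first shows whether participants did what they were asked, and the second shows how much of the planned protein was tolerated. Using only the original dose would label a participant who follows a protocol-directed reduction as non-adherent. Using only the dose in force would leave the reduction out of sight.

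The cost is the wording of one row and, if the diary has only a daily tick, one extra box for servings. The adherence figure will probably look less favourable. No dose or clinical rule changes.
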